### Allocation concealment

Allocation concealment will successfully be reached since no one involved in this study (i.e. the participants, researchers, and outcome assessors) will be aware of the treatment allocations. Furthermore, investigators will have no control over the order of patients randomized. A blinded investigator will encode the individuals and groups of intervention. To perform the allocation procedure, the encoded groups will be placed inside a closed opaque envelope, which will be labeled with the code for each participant. Envelopes will be opened only during the time of active or sham intervention.

### Intervention

All participants will attend the assigned rTMS intervention as follows: there will be ten sessions over two weeks, in which five sessions will be active and five will be sham, separated by a two-week washout period. The sessions will be administered consecutively and once a day. The researchers will be trained to perform both rTMS-sham and rTMS-active interventions.

#### rTMS-active

Over five consecutive sessions per week (i.e. one session daily), rTMS-active will be performed with a frequency of 5 Hz and 12 pulse trains. The stimulation intensity will be set at 100% of the motor threshold of the area corresponding to the *abductor pollicis brevis*. The stimulation target will be the area associated with the bilateral lower-limb motor area (i.e. vertex, Cz) of the M1.

We chose an intensity of 100%, based upon the limitations reported by Kumru et al. [16], who showed that an intensity of 90% applied during active rTMS was relatively low for leg muscles. In this line of reasoning, Rossini et al. [17] suggests that stronger descending excitatory drive shall be obtained by higher stimulus intensities, thereby yielding a faster temporal-spatial summation on cortico-motoneuron connections. We have also taken into consideration that some studies suggest the use of even higher intensities (some used 110–120% in individuals with Parkinson’s disease, for example) considering the elevated motor threshold of lower-limb muscles [33, 34]. The intensity of 100% was then chosen according the safety criteria suggested by Rossi et al. [9].

#### rTMS-sham

The rTMS-sham will be performed over five consecutive sessions per week (one session daily.) The sham coil will be used because it ensures the attenuation of the magnetic field while appearing to be the same shape as the active coil, with good approximation of auditory feedback [35]. In addition, the tactile contact of the coil with the skull is maintained.

### Procedures

The participants will be positioned comfortably in either a normal chair or a wheelchair, depending on the level of motor commitment of each patient. The feet will be positioned flat on the floor and the hands will rest on the thigh, in the supine position.

The rTMS stimulator will be connected to a figure-eight coil (i.e. butterfly coil) and positioned on the vertex of the lower-limb motor area, which corresponds to the apical surface of the skull. We chose to stimulate the vertex point because the motor impairment of subjects with iSCI occurs bilaterally, although the degree of involvement varies from one side to the other. Therefore, both cortical sides will be stimulated simultaneously, as the vertex point is equidistant between the left and right hemispheres [36, 37]. Standardized caps will be used, in accordance with the International 10-20 system EEG. Such a procedure will be used to find the motor threshold, a point which corresponds to the motor area of the *abductor pollicis brevis*, and so marks the point corresponding to the vertex.

### rTMS protocol

#### Magnetic stimulator

The rTMS will be applied using *Neurosoft - Neuro-MS 5* (Neurosoft Ltd®, Ivanovo, Russia), a commercially available transcranial magnetic stimulator equipped with an angulated figure-eight-shaped coil (AFEC – 01-100).

### Target

rTMS will be applied to an angulated figure-eight coil over the lower-limb motor area localized in M1 (in order to stimulate both lower limbs), with the handle of the coil parallel to the interhemispheric midline (pointing occipitally) as used by Khedr et al. [33], Jetté et al. [38], and Ji et al. [39] based on the vertex position of the International 10-20 system EEG.

When the orientation of the handle of a figure-eight coil is parallel to the interhemispheric midline (posterior–anterior direction), there is a TMS motor cortex activation through the preferential recruitment of cortical interneurons and through activating the pyramidal tract indirectly [17, 34, 40, 41]. Thus, the biological effect depends on the neuronal circuit finally recruited [17].

### rTMS sessions

Each session will be held at the Neuromodulation Laboratory of UEPB, using the same equipment during the same time of day. Each session will consist of 12 trains of 50 magnetic pulses at 5 Hz on each train. These pulses will be separated by 10-s intervals between each train. Intensity will be set at 100% of the individual’s RMT, defined as the lowest stimulation intensity that, within ten trials, induced at least five motor-evoked potentials assessed on the first dorsal interosseous muscle in the resting state. The parameters of rTMS were chosen based on safety parameters of the both National Institute of Neurological Disorders and Stroke (NINDS) and the paper by Rossi et al. [9].

### Primary outcomes

To evaluate the motor and sensory effects of the high-frequency rTMS in the lower-limb motor area on M1 (i.e. vertex, Cz) and check the possibility of generating motor gains in participants with iSCI, we will observe the change from baseline motor values provided by the ASIA score.

Only one researcher will be responsible for evaluating all of the participants through both the sensorimotor scales and electromyography (EMG). This researcher will be a physiotherapist who will also receive training to use the scales and EMG device. In addition, we will perform an evaluation of the intra-rater reliability of the instruments used in this study. Adverse events will be collected using a form for adverse events at each assessment point and any adverse event related to the intervention will be reported.

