**Fig. 1 Fig1:**
[figure not shown]
*Flowchart* for the rTMS study protocol. The participants will be selected and the eligibility assessment will be applied. They will then be randomized and allocated to group 1 (starting with rTMS-active) or group 2 (starting with rTMS-sham). Five sessions of rTMS-active and sham will be applied to participants in each group over one week, with a washout period (two weeks). Assessments will be before and after each intervention period (i.e. sham and active) using the motor and sensory scales, spasticity scale, and surface electromyography

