### Dropout criteria

Participants will be withdrawn from the study if they are not willing to continue their participation, cannot be present on the day of the experiment or miss a treatment section, and/or change their form of rehabilitation during the study.

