### Expected risks

High-frequency rTMS is a safe non-invasive technique according to current knowledge [9, 58]. Some studies indicate that there may be weak tension headaches and muscle spasms experienced during rTMS [59]. Overall, in cases where contraindications or safety parameters were not maintained, serious adverse events such as seizures occurred [9]. According to Rossi et al. [9], a large number of individuals were subjected to studies with rTMS since 1998 (when the limit parameters by Wassermann et al. [58] were defined) and a small number of seizures were observed. Therefore, the risk of rTMS-induced seizures is considered very low. To avoid adverse effects and risks to the individual, the rTMS parameters used in the present trial will be within the safety limits set by the NINDS and by Rossi et al. [9], which were updated security settings for transcranial magnetic stimulation.

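### Adverse-event forms are tied to four assessments rather than ten sessions or withdrawal, and the reporting commitment names related events, so events may be under-recorded

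*Protocol article*

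**What the plan says.** The only text on adverse-event collection is in the protocol article under Primary outcomes. It has two parts. On timing, with the start of the reporting clause: "Adverse events will be collected using a form for adverse events at each assessment point and any adverse event related to the intervention". The reporting clause in full is: "any adverse event related to the intervention will be reported". It names no judge of relatedness and no criteria, and it does not say whether events judged unrelated will be tabulated.

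The assessment points come from the Fig. 1 legend: "Assessments will be before and after each intervention period". Exposure is set under Intervention: "ten sessions over two weeks, in which five sessions will be active and five will be sham, separated by a two-week washout period". On the events anticipated, Expected risks says: "Some studies indicate that there may be weak tension headaches and muscle spasms experienced during rTMS". Under Dropout criteria, those withdrawn include participants who "cannot be present on the day of the experiment or miss a treatment section"; no safety form at exit is mentioned. Under Blinding, participants, researchers and outcome assessors are all to stay unaware of allocation.

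**The concern.** The form is scheduled around the efficacy assessments, while the events the article anticipates are mild, short-lived and occur under the coil. A form completed after the week asks the participant to remember five sessions, and minor events are easily forgotten over that span. Someone who stops, or misses a day, because of an event may leave before the next form is due.

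The reporting commitment then adds a second step, in which someone has to decide that an event was caused by the intervention. A sham-controlled crossover does not need that opinion, because participants who complete both periods supply a sham-period count to set against the active-period count. At stake is how complete the safety tabulation will be in a trial meant to inform clinical utility. In-session events that were never written down cannot be fully recovered later.

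**Working it through.** The article gives no adverse-event figure to reproduce, so the check compares schedules and then illustrates the relatedness step.

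**1. Forms against exposure.** Inputs: assessments before and after each of two periods (Fig. 1 legend); five active and five sham sessions (Intervention); 20 participants (Sample size).

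- Forms per participant: 2 × 2 = 4. The first precedes any stimulation.
- Sessions per participant: 5 + 5 = 10.
- Sessions per post-period form: 10 / 2 = 5.
- Whole trial, if all complete: 20 × 10 = 200 sessions against 20 × 2 = 40 post-period forms.

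The abstract mentions evaluations only at baseline and after each condition, which could be read as three assessments. The 2 × 4 analysis fits four. On either reading, one post-period form covers five sessions.

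**2. Withdrawal.** Inputs: 14 participants required, 20 recruited (Sample size). The implied allowance is (20 − 14) / 20 = 30%, or up to six people. This is a planning allowance, not an observed or stated rate. The article does not say how many would leave because of an event, or before their next form. Someone who leaves in the washout or in period 2 would normally have completed a form after period 1, so the gap concerns the period in progress at exit.

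**3. Relatedness.** If only events labelled related are reported, reported risk = true risk × share labelled related. The article gives neither quantity. The table assumes a true risk of 30% in both conditions and varies the share.

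| Share labelled related, active / sham | Reported risk, active / sham | Risk ratio (true value 1.0) |
|---|---|---|
| 90% / 90% | 27% / 27% | 1.0 |
| 50% / 50% | 15% / 15% | 1.0 |
| 90% / 70% | 27% / 21% | 1.29 |
| 90% / 50% | 27% / 15% | 1.80 |
| 70% / 90% | 21% / 27% | 0.78 |

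Any share below 100% lowers the reported rates. The ratio moves only when the shares differ between conditions, and it can then move either way.

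**The case against.** The strongest reply is that the sentence does not say only. Collection carries no relatedness filter, the form after each week can pick up session events by recall, and nothing excludes spontaneous reports or events that staff see. Reporting is not defined as publication and could mean notification. Session logs, exit forms and who decides causality are details that an article commonly leaves to the full protocol. Safety is neither the primary outcome nor a listed key secondary outcome.

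Much of this stands, and it limits the point to likely under-recording rather than certain loss. It does not remove the point, because the article is not silent: it states a collection schedule and names the class of events to be reported. Carried out as stated, these give a less complete count than the same form used at visits that take place anyway.

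A reader might go further and infer two things that the documents do not support.

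- **That the active-versus-sham safety comparison is biased.** Participants, researchers and assessors are to be blind, and equal attribution leaves the ratio at 1.0. The rTMS-sham section claims matching shape, approximate sound and skull contact, but not matching sensation, so unequal attribution is conceivable. Nothing in the article shows that it, or unequal withdrawal, will occur.
- **That seizures would go unrecorded.** Expected risks links seizures to cases where contraindications or safety parameters were not respected and calls the risk very low. Sessions are run by an experimenter in a laboratory, so a seizure there would be witnessed.

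**Conclusion.** The point holds as a modest, correctable weakness. Adverse-event forms are tied to four assessments while the anticipated events arise during ten sessions, no form is stated at withdrawal, and the reporting commitment rests on a causality judgement with no stated judge or criteria. The supported consequence is that brief in-session events and events preceding withdrawal may be under-recorded, and that reported rates may understate those collected.

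The documents fix only the structure: five sessions per post-period form, and a planned allowance of up to six of 20 participants leaving. The loss itself cannot be sized, because event rates, recall, the share judged related and the timing of withdrawals are not given; the risks tabulated above are illustrations under an assumed 30%. The conclusion assumes that the article's schedule is the one followed and that related means what it says. If the full protocol already provides session and exit recording and full tabulation, only the article's wording needs correcting.

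**What to change.** Three changes:

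- Have the person running each session complete the existing adverse-event form at that session, as well as its completion at the assessments.
- Complete the same form at any withdrawal, and record the reason for leaving.
- Commit to reporting all collected adverse events by condition (active or sham), whatever their judged relation. Keep relatedness as a descriptor, assigned by a named role blind to condition.

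The cost is a few minutes of recording per session: ten short forms per participant, or up to 200 across the trial, at visits participants already attend. Giving the task to the session operator avoids adding to the load of the single researcher who does all the scale and electromyography evaluations. Someone must also be given the relatedness rating. Treatment, outcomes and sample size are unchanged.

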#### ASIA – motor score

The International Standards for Neurological Classification of Spinal Cord Injury (ISNCSI) is a medical examination from which part of the ASIA motor score is derived [42]. It uses a test of the strength of ten key muscles on each side of the body (e.g. elbow flexors, wrist extensors, hip flexors, quadriceps, dorsi flexors). The score ranges from 0 (no contraction) to 5 (normal resistance) through a full range of motion. A total possible score of 50 for the upper extremities (UE) and 50 for the lower extremities (LE) may be obtained [42].

### Secondary outcomes

#### ASIA – sensory score

The ASIA sensory score is also part of the assessment for the ISNCSI [42]. The test involves pinprick and light touch sensation at key points representing each dermatome of the body, scored on a three-point scale (0, 1, and 2). Scores will be summed to give a total possible score of 224, where a higher score indicates better sensation than a lower score [42].

#### Fugl–Meyer scale for upper and lower members (motor part - FMS)

The FMS is an instrument used to evaluate body function impairment after stroke [43]. This scale assesses five domains: motor; sensory; balance; range of motion; and joint pain [43]. The UE (i.e. shoulder, elbow, forearm, wrist, and hand) and LE (i.e. hip, knee, and ankle) are assessed within the motor domain, then impairment severity and functional ability are indexed [44]. Sullivan et al. [44] affirm that it is likely that the FMS motor score may be a clinical measure indicative of white matter damage within CST fibers. This potential can justify its use in SCI populations. This scale is a 226-point multi-item Likert-type scale used to measure recovery. Multiple items are scored on a three-point ordinal scale (0 = cannot perform, 1 = perform partially, 2 = performs fully) [43]. In addition, the motor domain includes score ranges from 0 (plegia) to a maximum of 100 (normal motor performance); 66 points can be divided for the UE and 34 points for the LE [44, 45]. In this study we will only use the motor domain and evaluation will take place bilaterally.

#### Surface electromyography (EMG)

The EMG will be recorded differentially using round-shaped surface electrodes (Ag-AgCl, 0.8 cm diameter, with an inter-electrode distance of 2 cm) over the following muscles: vastus medialis; vastus lateralis; rectus femoris; biceps femoris; gastrocnemius; and tibialis anterior. We will position the electrodes at standard Surface ElectroMyoGraphy for the Non-Invasive Assessment of Muscles (SENIAM) positions [46], and a ground electrode will be over the tibia of the left leg. The EMG signals will be amplified and filtered (5 Hz to 2 kHz) by a biological data acquisition system Miotool 400 (Miotec®, Brazil) and sent to an A/D interface (National Instruments, Austin, TX, USA) with a 2-kHz sampling rate. Data will be stored on hard disk for later off-line processing. Data will be collected using the software *Miograph* (*Miotec*®). The EMG acquisitions will be obtained during knee extension, knee flexion, plantar flexion, and dorsiflexion. For 1 min, participants will perform contractile movements with speed controlled by audible and visual signals. The normalization procedure for peak contraction will be made to standardize EMG acquisitions and make them comparable.

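### The stated EMG filter (up to 2 kHz) and sampling rate (2 kHz) are incompatible, so any content between 1 and 2 kHz aliases into a secondary outcome; the likely effect is small

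*Protocol article*

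**What the plan says.** All the acquisition settings stand in the protocol article under Surface electromyography (EMG), which is listed among the secondary outcomes.

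- Recording: "The EMG will be recorded differentially using round-shaped surface electrodes (Ag-AgCl, 0.8 cm diameter, with an inter-electrode distance of 2 cm" (centimetres), over six leg muscles during knee and ankle movements.
- Filter: "The EMG signals will be amplified and filtered (5 Hz to 2 kHz".
- Digitisation: the filtered signal goes to an A/D interface "with a 2-kHz sampling rate".
- Processing: "Data will be stored on hard disk for later off-line processing". No further detail is given.
- Normalization: "The normalization procedure for peak contraction will be made to standardize EMG acquisitions and make them comparable".

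The section mentions no further low-pass filter ahead of the A/D step. It gives no noise level or EMG spectrum, and it does not name the EMG variable to be analysed. The primary outcome is a different measure. Under Primary outcomes the article says "we will observe the change from baseline motor values provided by the ASIA score", and the Sample size section bases its calculation on the motor score.

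**The concern.** A sampled signal represents frequencies only up to half the sampling rate. The low-pass filter ahead of the converter therefore has to cut off below that limit. Here the stated upper cut-off equals the sampling rate, which is twice the limit.

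Anything passed between 1 and 2 kHz is then recorded as if it were a lower frequency. Surface EMG is mostly low-frequency, so the folded content would be mainly broadband noise. Added noise raises the measured amplitude and shrinks proportional changes. It does so most where the EMG is weak, which can occur in people with incomplete spinal cord injury. Part of the contamination is fixed at acquisition and cannot be repaired later. What is at stake is the precision and sensitivity of one secondary measure.

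**Working it through.** The plan contains no computed figure to reproduce, so the check starts from the two stated settings.

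**Inputs from the article:** pass-band 5 to 2000 Hz; sampling rate fs = 2000 Hz.

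**Step 1, the limit.** Nyquist frequency = fs/2 = 2000/2 = 1000 Hz. The pass-band reaches 2000/1000 = 2 times this limit. A 2-kHz band would need sampling above 2 × 2000 = 4000 Hz.

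**Step 2, where the excess goes.** Alias frequency = |f − fs × round(f/fs)|.

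- 1200 Hz → 800 Hz
- 1500 Hz → 500 Hz
- 1800 Hz → 200 Hz
- 1995 Hz → 5 Hz

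So 1 to 1.5 kHz folds onto 500 to 1000 Hz, and 1.5 to 2 kHz folds onto 0 to 500 Hz. A digital 500-Hz low-pass removes the first part but not the second.

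**Step 3, amplitude under assumed spectra.** The article gives neither spectrum nor noise, so both are assumptions. The spectrum is P(f) ∝ f² / [(f² + fl²)(f² + fh²)²], with (fl, fh) from (30, 60) to (100, 300) Hz. White noise is set at 0 to 10% of EMG power over 5 to 2000 Hz. RMS inflation compared with an ideal 1-kHz cut-off is 1/√(1 − share of power above 1 kHz) − 1.

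| fl/fh (Hz) | Noise | Share above 1 kHz | RMS inflation |
|---|---|---|---|
| 30/60 | 0% | 0.02% | 0.01% |
| 100/300 | 0% | 1.58% | 0.80% |
| 30/60 | 10% | 4.57% | 2.37% |
| 100/300 | 10% | 5.99% | 3.14% |

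**Step 4, effect on a true 20% gain in amplitude.** Assumptions: RMS is the EMG variable, the noise floor is flat, no off-line filter is applied, and values are not normalized. Signal power is S, and noise power over 5 to 1000 Hz is 1. Folding raises the noise to (2000 − 5)/(1000 − 5) = 1995/995 ≈ 2. Measured gain = √[(1.44S + N)/(S + N)] − 1.

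- Signal RMS equal to noise RMS (S = 1). Compatible 1-kHz cut-off (N = 1): √(2.44/2) − 1 = 10.5%. As stated (N = 2): √(3.44/3) − 1 = 7.1%. Loss from aliasing alone: 3.4 points.
- Signal RMS five times noise RMS (S = 25). N = 1: √(37/26) − 1 = 19.3%. N = 2: √(38/27) − 1 = 18.6%. Loss: 0.7 points.

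**Step 5, how the two calculations relate.** With S = 25, RMS inflation is √(27/26) − 1 = 1.9%, inside the range in step 3. With S = 1 it is √(3/2) − 1 = 22%, far outside that range. The equal-RMS case is therefore an extreme, not a central estimate.

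**Step 6, adding a 500-Hz low-pass.** A low-pass before sampling leaves N ≈ 0.5. A digital one after sampling leaves about 0.5 true plus 0.5 folded, so N ≈ 1. For S = 1 the measured gains are √(1.94/1.5) − 1 = 13.7% before sampling and 10.5% after, a difference of about 3 points. For S = 25 they are √(36.5/25.5) − 1 = 19.6% and 19.3%, a difference of 0.3 points.

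**The case against.** The strongest defence accepts the mismatch and disputes that it matters. Most of that defence stands.

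- A reader might infer that the settings demonstrably blunt the EMG outcome. The article does not support this, because it gives no noise level, spectrum or EMG variable, so no loss can be derived from it. The largest loss above needs noise as strong as the signal, while the article describes recording during active contractions.
- A reader might infer that none of the contamination can be removed. Only the part from 1.5 to 2 kHz cannot be separated off-line. Processing steps are not described, and a condensed article need not describe them, so the absence of a digital low-pass cannot be assumed.
- A reader might credit the whole rise from 7.1% to 13.7% under a 500-Hz low-pass to curing aliasing. The step from 10.5% to 13.7% comes from narrowing the noise bandwidth, and the calculation ignores any true signal lost above 500 Hz.
- A reader might infer bias in favour of one condition. Each participant receives both conditions through the same recording chain, with a blinded assessor, so the added noise is non-differential.
- The hardware may in fact include a suitable anti-alias filter. If so, the recordings are sound and the stated 2-kHz cut-off is what needs correcting.

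One defence stands only in part. Normalizing to peak contraction cancels a constant scale factor, but it does not cancel additive noise. Noise power enters both numerator and denominator and pulls the ratio of a weaker contraction to the peak towards 1.

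**Conclusion.** The inconsistency is real and follows from two figures in one sentence; nothing else in the article resolves it. Either the recordings alias or the stated filter band is wrong.

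The consequence is minor. It can add noise to a secondary outcome and slightly shrink proportional changes. Under the assumed spectra and noise, RMS inflation is about 0.01% to 3%. On a true 20% gain, the loss from aliasing alone is about 0.7 points at a signal five times the noise and about 3 points at equality. These sizes rest wholly on assumed spectra, a flat noise floor and RMS as the variable. Confidence is high for the mismatch and low for any particular size. The comparison of active with sham is not biased by it, and neither the primary outcome nor the sample size depends on it.

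**What to change.** Check which filter and sampling settings the hardware actually applies. Then make the pair compatible in one of two ways:

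- keep 2-kHz sampling and set the anti-alias low-pass clearly below 1 kHz, for example 500 Hz, before the A/D step; or
- keep the 2-kHz band and sample above 4 kHz.

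Correct the stated pair in the EMG section. Recruitment may already be under way: Trial status gives a start in May 2017, although Table 1 gives December 2017 as first enrolment. Any change should therefore not fall between one participant's assessments. Hold the settings constant across both periods of each participant and report those used, including any participants recorded under different settings. If some recordings were made with the stated pair, a digital 500-Hz low-pass will remove part of the folded content; report that the rest remains.

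The cost is one setting and one line of text, plus larger files if the sampling rate is raised.
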